## Abstract

**Background:** Post-acute myocardial infarction (post-AMI) infection is an infrequent but important and serious complication in patients with ST-segment elevation myocardial infarction (STEMI) treated with percutaneous coronary intervention (PCI). Predicting its occurrence is essential for future prevention. However, little is known about the prediction of post-AMI infection in such patients to date. This study aims to develop and validate a new risk score based on risk factors for early prediction of infection in STEMI patients undergoing PCI.

**Methods:** This prospective, multi-center and observational study assesses the predictive value of risk score for post-AMI infection among a cohort of patients hospitalized due to STEMI. The STEMI patients undergoing PCI enrolled between January 1st 2010 and May 31st 2016 were served as a development cohort while those enrolled from June 1st 2016 to May 31st 2018 were served as validation cohort. The primary endpoint was post-AMI infection during hospitalization, defined as infection requiring antibiotics (reflecting the clinical influence of infection compatible with the necessity for additional treatment), and all-cause death and major adverse cardiovascular events (MACE) including all-cause death, recurrent myocardial infarction, target vessel revascularization, and stroke were considered as secondary endpoints. The risk score model based on risk factors was established using stepwise logistic regression, and will be validated in other centers and external patients with non-ST-elevation acute coronary syndrome (NSTE-ACS).

**Results:** This study will provide evidence on prognostic property, reliability of scoring, comparative performance, and suitability of the novel model for screening purpose in order to be recommended for clinical practice.

**Discussion:** Our study is designed to develop and validate a clinical risk score for predicting infection in participants with STEMI who have undergone PCI. This simple tool may therefore improve evaluation of post-AMI infection and enhance future researches into the best practices to prevent or reduce infection in such patients.

**Clinical Trial Registration:**
www.chictr.org.cn, identifier: ChiCTR1900028278.

## Introduction

ST-segment elevation myocardial infarction (STEMI) accounts for one-third of patients with acute coronary syndrome (ACS) worldwide, which resulted in poor outcomes and enormous financial losses every year (1). Post-acute myocardial infarction infection (post-AMI) is uncommon but is an important and serious complication in such patients. In addition, infections are crucial causes of morbidity and mortality and are associated with prolonged length of hospital stay and a substantial increase in health care costs (2, 3). Taking these undesirable effects into consideration, infection prevention has been one of the highest priorities for medical resources and government. Given that most infections are preventable, identification of STEMI patients at high-risk of infection could allow interventions to prevent and rapidly treat these infections among these patients.

Although some risk-prevention tools for mortality have been developed for STEMI patients, such as the Global Registry of Acute Coronary Events (GRACE) score (4) and the Thrombolysis in Myocardial Infarction (TIMI) risk score (5), there is no specific risk score for identifying STEMI patients undergoing percutaneous coronary intervention (PCI) to estimate the risk of post-AMI infection. In recent articles, we validated the age, creatinine and left ventricular ejection fraction (ACEF) risk score (6) and the Canada Acute Coronary Syndrome (CACS) risk score (7) for post-AMI infection, however, these scores were not developed specially for infection and the discriminatory accuracy were relatively low. In addition, various risk systems have been developed to predict infections following cardiac surgery (8, 9). Fowler et al. established a model that can identify patients undergoing cardiac surgery who were at high- risk for major infection (9). However, no study to date has validated a simplified scoring system to assess patients' individual risk of infection in STEMI patients undergoing PCI.

Given these data, this research protocol aims to develop and validate a practical risk score to identify the risk of post-AMI infection in patients with STEMI undergoing PCI. And this new risk score based on seven simple independent predictors would be divided into four levels according to the corresponding marks (low-, moderate-, high-, and very high-risk groups) to improve the clinical utility. Therefore, the present risk score could be easily applicable in clinical practice for identifying patients at high-risk of infection and in-hospital outcomes in patients with STEMI undergoing PCI and may help clinical decision-making allowing for timely measures to improve clinical outcomes.

## Materials and Methods

### Overview

We will follow the recommended procedures by the Prognosis Research Strategy (PROGRESS) Group (10–12) and show results according to the TRIPOD (Transparent Reporting of a Multivariable Prediction Model for Individual Prognosis or Diagnosis) statement (13, 14). In this research, we develop the risk score and perform the internal validation in patients admitted to Guangdong Provincial People's Hospital, and external validation is conducted in other centers and NSTE-ACS patients.

### Study Design

This proposed protocol involves a prospective, multi-center, observational cohort study (Figure 1). This study expected for enrollment from January 1st 2010 to May 31st 2018. Our study protocol has been approved by the ethics and research committee of Guangdong Provincial People's Hospital (GDREC2016378H) and was registered in the Chinese Clinical Trial Registry (www.chictr.org.cn, ChiCTR1900028278). This study will be designed and performed in accordance with the Code of Ethics of the 1964 Declaration of Helsinki and its later amendments. All enrolled patients will be required to provide written informed consent in this study. Contact information will be provided for participants for further enquiry.

**Figure 1 F1:**
[figure not shown]
Flow chart of study design.

### Study Oversight

The data safety committee has been guaranteed for this research, consisting of several cardiologists and one statistician. The cardiologists will be responsible for the review of the in-hospital course of the participants, while the statistician will conduct the safety analysis, and the data will be divided into development and validation cohorts.

### Study Population

STEMI was defined as the manifestation of typical chest pain and concomitant symptoms for ≥ 30 min but <12 h, with ST-segment elevation ≥ 1 mm in ≥ 2 continuous leads or new or undetermined duration of left branch bundle block accompanying with ≥ 2 times increase in troponin I or T (15).

The inclusion criteria were as follows: (a) age ≥ 18 years; patients with STEMI undergoing PCI, admitted to the cardiac intensive care unit; (b) patients could understand and agree with informed consent.

The exclusion criteria were as follows: (a) patients diagnosed with infection or treated with antibiotics prior to admission; (b) patients with tumor or chronic inflammatory diseases; (c) patients on hemodialysis at admission; (d) patients undergoing emergency cardiac surgery; (e) patients died within 24 h after admission; (f) readmission to hospital; and (g) patients with missing variables that are needed to calculate the risk scores.

Eligible patients were consecutively enrolled between January 1st 2010 and May 31st 2016, which were served as a development cohort. In accordance with the inclusion and exclusion criteria, patients enrolled from June 1st 2016 to May 31st 2018, with complete data regarding risk factors identified in the development cohort, will be served as a validation cohort. Furthermore, the patients screened according to the criteria in other centers will be enrolled for external validation.

To extend the application, this risk score will also be validated in our previous study including patients diagnosed with non-ST-elevation acute coronary syndrome (NSTE-ACS) following PCI according to the same exclusion criteria (16). This retrospective cohort study was designed to evaluate the association between parenteral anticoagulation therapy and clinical outcomes in patients mentioned above. Patients with principal discharge diagnosis of non-ST elevation myocardial infarction (NSTEMI) or unstable angina (UA) and underwent PCI during the index hospital stay were included. And patients with elevated cardiac biomarker and without new ST-elevation on ECG prior to index PCI were classified as NSTEMI while those were classified as UA if there were no positive cardiac biomarker findings and without new ST-elevation on ECG prior to index PCI (16).

### Laboratory Testing

Blood samples were obtained routinely and tested for electrolytes, white blood cell count, hemoglobin, cardiac enzymes, serum creatinine, blood lipids, serum albumin, total bilirubin, estimated glomerular filtration rate (eGFR) that was evaluated using the modified Modification of Diet in Renal Disease (MDRD) equation for Chinese people (17) and other routine laboratory parameters with 24 h after admission, while the medical history, the vital signs including body temperature, pulse rate, respiration rate and blood pressure, and Killip classification were also recorded at the same time.

### Procedure and Medications

All eligible participants received a conventional chest X-ray and ultrasonic cardiography. The left ventricular ejection fraction (LVEF) was measured by echocardiography after admission. Furthermore, blood cultures were examined at the discretion of the responsible physicians. Before the procedure, administration of 300 mg aspirin and 180 mg ticagrelor or clopidogrel (300 or 600 mg) were mandatory for all included patients. PCI was performed by the interventional cardiologists in the conventional manner, and coronary stents were, or other procedures were used when required. Hydration with intravenous normal saline solution at a hydration rate of 1 ml/kg/h or 0.5 ml/kg/h if the LVEF was <40% was initiated during the procedure and maintained until 6 to 12 h after the procedure. After completion of this procedure, lifelong aspirin (100 mg/day) was prescribed and at least 12 months of clopidogrel (100 mg/day) or ticagrelor (90 mg twice/day) were recommended to all patients. Additionally, the prescription of anticoagulants, β blockers, glycoprotein IIb/IIIa inhibitors, or angiotensin-converting enzyme inhibitors/ angiotensin receptor blockers (ACEI/ARB) was at the discretion of the operators according to current guidelines.

### Data Collection and Missing Data

Clinical data including patient demographics, diagnosis, medical histories, clinical and laboratory characteristics, medication treatment, procedural details and main outcomes were obtained through review of electronic medical records. The principal data, such as clinical outcomes, were collected by two investigators independently, and inconsistent data were verified by a third investigator.

Variables were included as candidates for this risk score after removing variables with ≥ 10% missing values (Table 1), and for those with incomplete data, we assumed that patients with the missing data ≤ 5% occurred at random depending on the clinical variables and used multiple imputations. This risk score model was developed based on imputed complete cases.

**Table 1 T1:** Observations and endpoints.

**Category**	**Method and materials**	**Observation and examination items**
Demographic characteristics	Interview	Age, sex and smoking status.
STEMI	Medical examination and interview	Onset of STEMI, date of hospitalization, description of treatment.
History of present illness/previous history/therapies	Interview	Previous history of cardiovascular and cardiovascular risk-related diseases and history of treatment (Hypertension, MI, CABG, COPD, AF, stroke, PCI, sudden cardiac arrest, thrombolysis, pericardial effusion, PCI lesion).
Physical findings	Medical examination	SBP, DBP, heart rate and Killip class.
Family history	Interview	Coronary artery diseases, hypercholesterolaemia and ischaemic cerebral infarction in relatives to the second degree of kinship.
Hematological and biochemical examinations	Serum and urine	The following parameters will be measured from blood acquired within 24 h after admission: WBC, eGFR, creatinine, albumin, hemoglobin, TG, TC, total bilirubin, direct bilirubin, LDL, HDL, ALT, CO_2_ combining power, Urine PH.
Heart function	Echocardiography	LVEF, LVDd, LVDs.
Medication during hospital stay	Electronic medical record	Statins, Warfarin, Tirofiban, ARB, CCB, ACEI, β-blockers, insulin, metformin, PPI, diuretics and nitrates.
Procedural characteristics	Electronic medical record	PCI approach, multi-lesion, contrast volume, number of stents and total length of stents.
Primary endpoint	Interview	Post-acute myocardial infarction infection during hospital admission and the type of infections (pulmonary infections, urinary infections or others including abdominal sepsis, primary bacteremia, and unidentified primary infection sites).
Secondary endpoints	Interview	Presence or absence events: in-hospital all-cause mortality and major adverse cardiovascular events (MACE) including all-cause death, recurrent myocardial infarction, target vessel revascularization, and stroke.

*STEMI, ST-segment elevation myocardial infarction; MI, myocardial infarction; CABG, coronary artery bypass graft; COPD, chronic obstructive pulmonary disease; AF, atrial fibrillation; PCI, percutaneous coronary intervention; SBP, systolic blood pressure; DBP, diastolic blood pressure; WBC, white blood cell; eGFR, estimated glomerular filtration rate; TG, triglycerides; TC, total cholesterol; LDL, low-density lipoprotein; HDL, high-density lipoprotein; ALT, alanine aminotransferase; LVEF, left ventricular ejection fraction; LVDd, left ventricular end-diastolic diameter; LVDs, left ventricular end-systolic diameter; ARB, angiotensin receptor blockers; CCB, calcium channel blockers; ACEI, angiotensin converting enzyme inhibitors; PPI, proton pump inhibitor*.

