#### Data Analysis

The student's *t*-test or Wilcoxon rank-sum test was used to compare the continuous variables and the chi-square test or Fisher exact test was used as appropriate for categorical variables for the comparison of patients with or without infections in both datasets.

The risk score was developed using a backward stepwise logistic regression model. All candidate predictors were included in the development of the risk score, and to avoid overfitting data and select the best subset of risk factors, a bootstrap method was used. For missing data, 10 multiple imputations were performed using the SAS MI procedure, and 100 bootstrap repeats were conducted for each imputation. Variables selected in at least 90% of 1,000 bootstrap repeats were included in the final model. The risk score was developed for each imputed data via using the selected variables and the SAS MIANALYZE procedure was used to combine the results of the analyses. For this risk score, the scoring method was analogous to that of Sullivan et al. (21) and was used based on the developed risk score. For the scoring purpose, continuous variables were categorized into groups regarding the clinical significance. The risk score of post-AMI consisted of four levels (low-risk, moderate-risk, high-risk, and very high-risk) in order to enhance the clinical utility.

Both discriminatory accuracies assessed by the C-statistic and calibration measured by the Hosmer-Lemeshow χ^2^ statistic and calibration plot were used to evaluate the predictive accuracy of the risk score. The bootstrap method with 1,000 bootstrapped replications was used to perform an internal cross-validation of the risk score. The average of the C-statistic was reported. In addition, external validation and subgroup validation (older, gender, diabetes, anemia, and chronic kidney disease) of the risk score model was conducted to assess the stability of the model. The risk score was also validated in patients with NSTE-ACS undergoing PCI, and the area under curve (AUC) of this risk score was compared to the previous scoring systems (6, 7). Furthermore, comparison of the area under the receiver operating characteristic (ROC) curve was according to the nonparametric approach of DeLong et al. (22). To evaluate the clinical utility of this risk score, decision curve analysis was introduced and the risk score with a higher net benefit indicated a better clinical effect (23).

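### Drugs recorded at any time during the stay are candidates for an early-prediction score, and no rule requires a predictor to precede infection

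*Protocol article*

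**What the plan says.** The abstract gives the aim as a "new risk score based on risk factors for early prediction of infection in STEMI patients undergoing PCI".

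Under Data Collection and Missing Data, the candidate rule is "Variables were included as candidates for this risk score after removing variables with ≥ 10% missing values (Table 1"). The Data Analysis section adds: "All candidate predictors were included in the development of the risk score". Backward stepwise logistic regression follows, and a variable is kept if it is selected in at least 90% of 1,000 bootstrap repeats.

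One row of Table 1 is "Medication during hospital stay". It lists 12 drugs: statins, warfarin, tirofiban, ARB, CCB, ACEI, β-blockers, insulin, metformin, PPI, diuretics and nitrates. No start date or cut-off is attached.

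Other rows do have a clock. Table 1 and Laboratory Testing tie blood results to the first 24 h after admission, and Laboratory Testing says vital signs and Killip class were recorded at the same time. The primary endpoint is any infection needing antibiotics during the hospital admission.

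**The concern.** Predictor and outcome are both defined over the whole stay, and nothing puts them in order. This raises two problems.

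- **Reverse direction.** A patient who becomes infected and deteriorates may be started on insulin, diuretics or a PPI as a result. In the data the drug then looks like a predictor of infection when it is a consequence.
- **Availability.** A variable that means given at some point during the stay is not settled until discharge. It cannot feed an early score, even if no drug was ever started because of infection.

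The planned safeguards are not aimed at this. Bootstrap selection and bootstrap validation resample the same records. The validation cohort of June 2016 to May 2018 would reproduce the association if drugs were recorded in the same way. Discrimination could look good throughout for a score that cannot be calculated when it is needed.

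**Working it through.** **The plan's own figure.** Sample Size Consideration: 10 events per variable × 8 risk factors = 80 infections, and 80 / 0.10 = 800 patients. This reproduces exactly. The concern does not depend on it, but it sets the scale for the illustration.

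**Timing of each Table 1 group against the outcome**

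| Group | Stated time limit |
|---|---|
| Blood results, vital signs, Killip class | first 24 h after admission |
| Drugs | the whole stay |
| Outcome | the whole stay |

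The conflict with early prediction follows from these lines alone, with no arithmetic.

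**Illustration of size.** The documents give no drug-use rates, so *b* and *s* below are assumptions. Let *b* be use among patients without infection and *s* the share of infected non-users who start the drug after onset. The drug has no true predictive value.

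- Use among infected: π = b + (1 − b)s
- Odds ratio: [π/(1 − π)] / [b/(1 − b)]
- Single-variable C: 0.5 + (π − b)/2

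With b = 0.30:

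| s | π | OR | C |
|---|---|---|---|
| 0.2 | 0.44 | 1.83 | 0.57 |
| 0.3 | 0.51 | 2.43 | 0.605 |
| 0.4 | 0.58 | 3.22 | 0.64 |

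**Does the 90% rule screen it out?** Take a univariable Wald test at p<0.05, with 80 infected and 720 uninfected patients. For s = 0.3 the expected cells are 40.8, 39.2, 216 and 504. So log OR = 0.887, SE = √(1/40.8 + 1/39.2 + 1/216 + 1/504) = 0.238, and expected z = 3.73.

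To be selected in 90% of bootstraps, the observed z must be about 1.96 + 1.28 = 3.24. The chance of that is Φ(3.73 − 3.24) = Φ(0.49), about 69%. For s = 0.2 the expected z is 2.53, which gives Φ(−0.71), about 24%.

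A simulation (300 studies of 800 patients, 10% infected, 200 bootstraps each) gave these pass rates:

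| Baseline use | s = 0 | s = 0.1 | s = 0.2 | s = 0.3 | s = 0.4 |
|---|---|---|---|---|---|
| 10% | 0% | 19% | 80% | 98% | 100% |
| 30% | 0% | 3% | 24% | 62% | 92% |
| 50% | 0% | 0.3% | 5% | 25% | 62% |

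The rule rejects a useless drug when there is no leak. It gives no dependable protection when there is one.

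**The case against.** **Table 1 is not a clean candidate list.** It is titled as observations and endpoints, and it contains dates and the outcomes themselves, so not every row can be a candidate. This stands as a caution. Even so, the candidate rule cites Table 1, and no passage takes the medication row out.

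**No leak is shown.** The Introduction speaks of seven simple predictors without naming them. A reader might infer that the score is already contaminated, but the article does not support that. The claim is limited to what the stated rule allows.

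**Not all 12 drugs are plausible consequences of infection.** Procedure and Medications leaves glycoprotein IIb/IIIa inhibitors, β-blockers and ACEI/ARB to the operators, which suggests prescribing around the PCI. So 12 drugs counts the row, not the leaking variables. The availability problem still applies to any drug defined over the whole stay.

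**LVEF.** It is tempting to add LVEF, since "The left ventricular ejection fraction (LVEF) was measured by echocardiography after admission" has no upper limit. But the hydration rule, "0.5 ml/kg/h if the LVEF was <40% was initiated during the procedure", implies that a value was known by the procedure. The article does not say which measurement feeds the score. That calls for confirmation and is not a second defect.

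**Diabetes.** A reader might also make something of diabetes, which is planned as a subgroup but not named in Table 1. The history row covers risk-related diseases in general terms, and a condensed list is not an error.

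**The illustration is simplified.** It is univariable and assumes p<0.05, while the plan uses backward stepwise selection and states no retention threshold. This stands. The figures show that the mechanism can matter and do not forecast how often it would.

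**Conclusion.** The point holds for the medication row and the missing prediction time. The article fixes a candidate rule that, followed as written, admits variables measured over the same window as the outcome. That conflicts with the aim of early prediction. It is a conflict between stated rules, not a detail left to a fuller document.

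The size depends on assumed drug-use rates. Where 20% to 40% of infected non-users start a useless drug used by 30% at baseline, it alone gains a C of 0.57 to 0.64 and passes the 90% rule in about 24% to 92% of studies. Among the other combinations, the pass rate is about 5% with 50% baseline use and 20% starting, and 98% with 10% baseline use and 30% starting. If only 10% start, it is at most 19%. A reader might infer that such a drug is certain to be selected, but these figures do not support that. The inflation of accuracy is conditional on a drug being selected.

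**What to change.** 1. State one prediction time. 24 h after admission would match the laboratory window and the existing exclusion of patients who die within 24 h.
2. Restrict candidates to information known by that time and before infection onset, and say how patients infected earlier are handled.
3. Remove the in-stay medication row from the candidates. Use admission or pre-admission drugs only if they are already in the records.
4. Confirm that the LVEF used is the one available by the prediction time.
5. If the seven predictors are already chosen, name them and check each against this rule. If any is an in-stay drug, repeat the selection.

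**Cost.** Dropping the row is an edit to the candidate list and needs no new patients. Pre-admission drugs are not a listed Table 1 item and enrolment of both cohorts ended by May 2018, so that option could mean going back to the records. The apparent C may fall slightly.
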